**Psychological factors**									
	PCS-6^f^		A short form of the Pain Catastrophizing Scale that measures catastrophic thinking about pain. It consists of 6 items across 3 subscales—2 items each for “rumination,” “helplessness,” and “magnification”—each scored from 0 to 4, yielding a total score of 0-24, with higher scores indicating greater catastrophic thinking [34,35].					Internal consistency: Cronbach α=0.88 Correlation with the full 13-item PCS: r=0.94 in individuals with chronic pain conditions	
	TSK-11^g^					Measures fear of movement using 11 items from 1 (“strongly disagree”) to 4 (“strongly agree”), yielding a total score of 11-44. Scores <22 indicate minimal fear, 23-28 low fear, 29-35 moderate fear, and ≥36 high fear [36,37].		Convergent validity: association with pain catastrophizing, severity of expected pain with movement, and willingness to complete tendon loading exercises in individuals with Achilles tendinopathy Test-retest reliability: ICC=0.81 (in individuals with back pain)	
	PHQ-2^h^		Screens for depression over the past 2 weeks using 2 items scored from 0 (“not at all”) to 3 (“nearly every day”), yielding a total range of 0-6. Scores of 0-2 suggest minimal or no depression, while scores ≥3 indicate possible depression requiring further evaluation [36].					Sensitivity: 83% Specificity: 92%	
	PROMIS^b^ Sleep Disturbance					Evaluates sleep quality and disturbances across 8 items, each scored from 1 (“not at all”) to 5 (“very much”), yielding raw scores of 8-40. Scores are converted to T-scores (mean 50, SD 10), ranging approximately from 20 to >80. T-scores of 55-60 indicate mild sleep disturbance, 60-70 suggest moderate disturbance, and >70 reflect severe sleep disturbance [37,38].		Internal consistency: Cronbach α=0.96 Convergent validity with the Pittsburgh Sleep Quality Index: r=0.85 Test-retest reliability: ICC=0.62-0.71 (in fibromyalgia populations)	
	PROMIS^b^ Self-Efficacy for Managing Symptoms 8a			Assess the subject’s level of confidence in managing their symptoms in different settings (home, public place, and an unfamiliar place) and in keeping their symptoms from interfering with work, sleep, relationships, or recreational activities. Each item scored from 1 (“not at all confident”) to 5 (“very confident”), yielding raw scores from 8 to 40. Converted T-scores below 30 suggest very low, 30-40 low, 40-60 average, 60-70 high, and 70-80 reflect very high self-efficacy [39].					Internal consistency: Cronbach α=0.92 Correlations with Chronic Pain Self-Efficacy Scale: r=0.74 (in patients with chronic conditions)
	GAD-2^i^			Screens for generalized anxiety disorder by asking about the frequency of feeling nervous and unable to control worrying over the past 2 weeks. It uses 2 items, each scored from 0 (“not at all”) to 3 (“nearly every day”), totaling 0 to 6. Scores of 0 to 2 indicate minimal or no anxiety, while scores of 3 or higher suggest possible anxiety requiring further assessment [40].					Sensitivity: 76% Specificity: 81% Internal consistency: Cronbach α=0.89
**Comorbidities**									
	TAPS-1^j^			Screens for substance use in the past 12 months. Scores range from 0 to 4 (0=“never” and 4=“daily or almost daily”) for each substance category, with higher scores indicating more frequent use [41].					Sensitivity: 81%-96% Specificity: 78%-91%
	CCI^k^					Predicts 10-year mortality for patients with multiple comorbidities based on 19 weighted conditions, scored from 1 to 6 points, with a total range of 0 to >37. Higher scores correspond to a greater comorbidity burden [42-44].		Test-retest reliability: ICC=0.94 (for self-report data compared to chart reviews) Inter-rater reliability: ICC=0.80	
	WPI^l^					Assesses pain distribution across 19 body areas, assigning a score of 0 if there is no pain and 1 if pain is present in each area. A total score of 7 or more typically indicates widespread pain. The SSS^m^ scale evaluates symptom severity in 2 components: the first assesses fatigue, unrefreshing sleep, and cognitive difficulties, while the second derives a general symptom severity score based on the number of symptoms reported from a list of 41 symptoms. Patients receive a score of 0 for no symptoms, 1 for 1-10 symptoms, 2 for 11-24 symptoms, and 3 for 25 or more symptoms. The total SSS score ranges from 0 to 12, calculated by summing the scores from the first component (range 0-9) and the second (range 0-3) [45].		Internal consistency: Cronbach α=0.34 for the WPI, 0.83 for the SS, and 0.82 for the combined use of both tools. Sensitivity: 100% and Specificity: 81% for WPI Sensitivity: 89.2% and Specificity: 83.8% for SSS	

^a^PEG: Pain, Enjoyment, General Activity.

^b^PROMIS: Patient-Reported Outcomes Measurement Information System.

^c^ICC: intraclass correlation coefficient.

^d^FAAM: Foot and Ankle Ability Measure.

^e^VISA-A Sedentary: Victorian Institute of Sport Assessment–Achilles (sedentary version).

^f^PCS-6: Pain Catastrophizing Scale–6.

^g^TSK-11: Tampa Scale for Kinesiophobia–11.

^h^PHQ-2: Patient Health Questionnaire–2.

^i^GAD-2: Generalized Anxiety Disorder–2.

^j^TAPS-1: Tobacco, Alcohol, Prescription medication, and other Substance use.

^k^CCI: Charlson Comorbidity Index.

^l^WPI: Widespread Pain Index.

^m^SSS: Symptoms Severity Scale.

#### Movement Tasks

Pain intensity will be reported using the numeric rating scale (NRS), where 0 indicates no pain, and 10 indicates the worst pain imaginable [46,47]. The NRS has been shown to have excellent test-retest reliability (intraclass correlation coefficient=0.95) and concurrent validity with good-to-excellent correlation with the visual analog scale (r=0.941) [48]. Participants will rate their level of pain at rest. In addition, they will report their heel pain (plantar fascia or Achilles tendon, depending on group assignment) during the following three movement tasks: (1) the “Windlass test” will be performed in a standing position with passive extension of the participant’s great toe to the end range while bearing weight on the affected foot. A positive test will be indicated by reproduction or exacerbation of plantar heel pain [5,49]. The weight-bearing Windlass test demonstrates 100% specificity and 31.8% sensitivity [49]; (2) for the “single-leg heel raise test,” participants will stand on the affected leg with their fingertips on a wall in front of them to provide balance. Keeping the knee straight, they will then lift and lower their heel as high as possible. They will perform as many repetitions as they can while keeping pace with a metronome beat played from a phone application (60 Hz). The task will continue until muscle fatigue or symptom exacerbation prevents further movement. The test will be discontinued if the participant is unable to maintain proper technique, such as bending the knee, flexing the trunk, or failing to keep pace with the metronome. If a participant is unable to perform single-limb heel raises, the test will be modified to a double-limb heel raise, instructing them to shift as much weight as possible onto the involved side [5,50,51]; and (3) the “single-leg drop landing test” will be conducted by asking participants to step onto a platform while leading with their affected leg and then step back down, landing only on the affected foot [52]. If this movement does not provoke pain or symptoms, participants will be instructed to add a vertical jump immediately after landing on the involved foot [53].

#### Trigger Point Identification

Participants will lie in the prone position with knees flexed at 15° and ankles in their naturally relaxed plantarflexed posture. A physical therapist will examine 5 muscles: 3 in the calf (medial gastrocnemius, lateral gastrocnemius, and medial soleus) and 2 in the foot (abductor hallucis and flexor digitorum brevis). To facilitate consistency in the examination and imaging, the assessment will be limited to the following muscle zones, which Simons [54] has described as common trigger point locations.

Calf zones will be centered at 50% of the leg length measured from the fibular head, with the gastrocnemius zone extended proximally by 40% of the leg length, while the soleus zone will be extended distally by 30% of the leg length. For foot muscles, the abductor hallucis zone will be centered along a vertical line from the anterior medial malleolus, with medial and lateral boundaries extending 5% of the leg length [55]. The flexor digitorum brevis zone will begin 2 cm distal to the medial calcaneal tubercle and span 10% of the leg length distally. Leg length will be measured from the fibular head to the lateral malleolus. Using standardized zones based on leg length ensures that similar regions of the muscle belly are captured and helps ensure that the distance between the most proximal and distal trigger points is no greater than 20 cm, which corresponds to the MRI field of view.

The physical therapist will palpate within the 5 zones to determine if a trigger point is present and mark the tautest band using a waterproof marker in a cross shape in each zone. This approach allows for the same locations to be assessed with ultrasound imaging and MRI. Trigger point identification will follow the gold standard diagnostic criteria established by Simons [54], who defines a trigger point as a taut band of skeletal muscle that is tender to palpation. The physical therapist will apply constant pressure with palpation for 5 seconds on the most tender taut band in each of the 5 zones, with a 20-second rest between each spot. Participants will be asked whether the pressure reproduces the same heel pain [54] and whether the pain is felt locally at the site of palpation or referred to another area [10] at each site. For comparison of imaging outcomes between trigger points and healthy tissue, at least 1 of the 5 marks will indicate healthy tissue using the same cross shape. Imaging researchers will remain blinded to the trigger point versus healthy tissue identification to ensure unbiased image acquisition.

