## Introduction

Plantar heel pain, the most common source of foot pain, affects approximately 1 out of every 10 adults and accounts for approximately 2 million medical visits annually in the United States [1,2]. Individuals with plantar heel pain frequently experience reduced quality of life and diminished satisfaction with activities of daily living [3,4]. Plantar heel pain is characterized by pain along the sole, most noticeable during initial steps following a period of inactivity and during prolonged weight-bearing activities [5]. The term “plantar fasciitis” is often used to describe this condition and suggests inflammation as the main cause of heel pain. However, the broader term “plantar heel pain” is preferred, reflecting the multifactorial nature of the underlying causes—including myofascial changes, adjacent tissue pathology, and psychosocial factors [5-9].

One potentially underrecognized component of plantar heel pain is myofascial pain, which is characterized by the presence of trigger points in the calf and foot muscles that can reproduce the individual’s pain [10,11]. Trigger points are defined as hypersensitive areas within a tight band of skeletal muscle that elicit local or referred pain when compressed, contracted, or stretched. The current standard for diagnosing myofascial pain relies on a clinical examination using manual palpation [12,13], which lacks objectivity and quantitative precision. Identifying a diagnostic imaging biomarker [14] for trigger points could significantly improve the accuracy of diagnosing myofascial pain and inform targeted treatment strategies.

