## Methods

### Participants

This cross-sectional study will enroll a total of 100 participants, including 50 individuals diagnosed with plantar heel pain, along with 2 control groups. The first control group will consist of 25 individuals with insertional Achilles tendinopathy, for whom targeted myofascial treatments are not considered first-line interventions [23]. The second control group will include 25 pain-free individuals with a similar age, BMI, and sex distribution as the plantar heel pain and insertional Achilles tendinopathy groups. To ensure balanced representation, enrollment will be structured so that neither sex comprises more than 60% of each group. Eligibility and group assignment will be based on the inclusion and exclusion criteria outlined in Textbox 1. Screening for study eligibility will occur in three phases: (1) an online screening form, (2) a video visit with a physical therapist, and (3) an in-person clinical examination by a physical therapist. Individuals who provide informed consent and meet all criteria will be enrolled in this study.

Eligibility criteria.

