#### Clinical Examination

The clinical examination will be performed by a physical therapist with advanced training in dry needling for myofascial pain and will include (1) movement tasks, (2) trigger point identification, and (3) pressure pain threshold testing. In addition, participants will complete a series of patient-reported outcome measures. These outcomes align with the HEAL Common Data Elements and are supplemented by additional psychological surveys, as well as foot- and ankle-specific pain and function outcomes [25] (Table 1).

**Table 1 table1:** Patient-reported outcome measures.

Outcome							Description		Psychometrics

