### MRI

To ensure spatial alignment between clinical examination, ultrasound imaging, and MRI, magnetic resonance–visible fiducial markers will be placed over the marked trigger points identified during clinical examination. MRI will be conducted using a 3T whole-body MRI (Signal Premier, GE Healthcare). Scanning will begin using an 8-channel foot-ankle receive RF coil (GE Healthcare, Waukesha) for imaging the foot, followed by a 32-channel flexible blanket array receive RF coil (GE Healthcare) for imaging the calf. Imaging will be performed on the affected side in participants with plantar heel pain and insertional Achilles tendinopathy, and on a single side in pain-free controls, with all participants scanned in the supine position with slight knee flexion and ankle plantar flexion to accommodate a 1.5-inch heel lift between the heel and the RF coil (approximately 20° of plantar flexion).

The imaging will include the following sequences: T2-weighted fast spin-echo sequences for T2 mapping and evaluation of inflammation and cysts [66]; zero echo time proton density sequences to detect bony abnormalities [67,68]; quantitative T1ρ imaging, which provides sensitivity to multiple features such as chemical exchange between extracellular water, macromolecules and pH [69,70]; chemical shift–encoded Iterative Decomposition of water and fat with Echo Asymmetry and Least-squares estimation for T2* and fat fraction quantification to assess tissue composition [71,72]; intravoxel incoherent motion (IVIM) diffusion imaging to evaluate tissue perfusion; and T1-weighted imaging to measure plantar fascia and fat pad thickness.

MRI data will be analyzed using both quantitative and qualitative approaches. Regions of interest (ROI) will be measured based on the fiducial markers corresponding to the locations identified during the clinical examination. Water and fat images will be generated using the Iterative Decomposition of water and fat with Echo Asymmetry and Least-squares estimation (IDEAL) for the separation of fat and water species [71, 72], Specifically, these will be produced using the vendor supplied chemical shift–encoded 3D gradient-echo sequence (IDEAL-IQ, GE Healthcare, WI, USA).

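### No stated blind covers the therapist who sets the palpation label, or covers group, so the pooled primary AUC can credit biomarkers that merely differ by group

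*Protocol article*

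**What the plan says.** In the protocol article, Clinical Examination gives one role the whole examination: "The clinical examination will be performed by a physical therapist with advanced training in dry needling for myofascial pain". Its listed parts are, in order, the movement tasks, the search for trigger points and the pressure pain threshold test. Movement Tasks then says of participants that "they will report their heel pain (plantar fascia or Achilles tendon, depending on group assignment) during the following three movement tasks". Under Trigger Point Identification the physical therapist palpates five zones, decides whether a trigger point is present, and asks whether pressure brings on the participant's own heel pain. Under Participants, the last screening step is also "3) an in-person clinical examination by a physical therapist"; it is not said to be a different person.

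Two blinds are stated. Trigger Point Identification says: "Imaging researchers will remain blinded to the trigger point versus healthy tissue identification to ensure unbiased image acquisition". Ultrasound Imaging blinds shear wave analysts to the velocity overlay. Neither mentions the labelling examiner, and neither mentions group.

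Data Analysis makes the AUC for tissue with and without myofascial pain the primary performance measure, pooled over the five muscles of each participant. It ranks 20 candidates and takes up to five into the biosignature. The Introduction says that diagnosis "relies on a clinical examination using manual palpation [12,13], which lacks objectivity and quantitative precision". Limitations discusses only the lack of an agreed trigger point definition.

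**The concern.** Each AUC is only as good as the label that it is scored against. Here the label is a judgement that the article itself calls not objective. It is made by someone who, to ask about the right pain site, very probably has to know whether the participant has plantar heel pain, Achilles tendinopathy or no pain.

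An examiner who expects trigger points in plantar heel pain, and few in controls, may settle borderline bands accordingly. The label then carries group information that is not in the tissue. Because the AUC compares positive and negative sites across groups, a biomarker that differs by group for another reason is credited with detecting trigger points. Blinding imaging staff to the site label does not prevent this, because the bias lies in the reference and not in the image. As the top candidates are then selected by rank, even a small shift could change which are chosen.

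**Working it through.** **The plan's own precision figure, as a yardstick.** Sample Size states a 95% CI half-width of 0.10 at AUC 0.70, with five muscles, an intraclass correlation of 0.5 and 36% prevalence in plantar heel pain.

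- Design effect: 1 + (5 − 1) × 0.5 = 3.
- Hanley-McNeil: SE² = [A(1−A) + (n₁−1)(a−A²) + (n₀−1)(b−A²)] / (n₁n₀), with a = A/(2−A) and b = 2A²/(1+A). Site counts are divided by 3.
- Plantar heel pain gives 250 × 0.36 = 90 positive sites. Control prevalence is not given, so it is varied:

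| Sites used | Effective positive / negative | Half-width |
|---|---|---|
| Plantar heel pain only | 30.0 / 53.3 | 0.121 |
| All 100, controls 0% | 30.0 / 136.7 | 0.112 |
| All 100, controls 10% | 38.3 / 128.3 | 0.101 |
| All 100, controls 18% | 45.0 / 121.7 | 0.095 |
| All 100, controls 36% | 60.0 / 106.7 | 0.086 |

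The stated 0.10 lies inside this range and is not disputed.

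**Illustration of label drift.** All inputs are assumptions except the group sizes (250 plantar heel pain sites, 250 control sites).

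- True prevalence is 25% in every group. A fraction f of negative sites in plantar heel pain is called positive, and the same fraction of positive control sites is missed.
- Recorded prevalence: plantar heel pain 0.25 + 0.75f; controls 0.25(1 − f).
- The biomarker is normal with SD 1, differs by d between plantar heel pain and controls, and is unrelated to the label within each group. Its true AUC is 0.50.
- Let w₁ and w₀ be the plantar heel pain share of recorded positive and negative sites. Then AUC = 0.5 + (w₁ − w₀)(Φ(d/√2) − 0.5).

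At f = 0.10, recorded prevalences are 0.325 and 0.225. So w₁ = 0.325/0.550 = 0.591, w₀ = 0.675/1.450 = 0.466, and the difference is 0.125. At f = 0.20 they are 0.40 and 0.20. So w₁ = 0.667, w₀ = 0.600/1.400 = 0.429, and the difference is 0.238.

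| Drift f | d = 0.5 | d = 0.8 | d = 1.2 |
|---|---|---|---|
| 0 | 0.500 | 0.500 | 0.500 |
| 10% | 0.517 | 0.527 | 0.538 |
| 20% | 0.533 | 0.551 | 0.572 |

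Against the planned half-width of 0.10, the largest shift is 0.038 at 10% drift and 0.072 at 20%. In this model the AUC within each group stays at 0.50, because the biomarker and the label are linked only through group.

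**The case against.** Much can be said for the plan.

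- **The examiner's knowledge is inferred.** No sentence says that the therapist knows the group. A reader might infer that the therapist runs different pain tasks in each group; the three tasks are the same for all, and only the pain site rated differs. The inference is strong, but it remains an inference. The article is also condensed, and examiner masking may be described in the full protocol. The point therefore rests on the scope of the blinds that are stated.
- **There are real safeguards.** The Figure 1 legend puts the label before imaging, so the image cannot influence it. Zones are standardised, tenderness is partly the participant's own report, and at least one mark per participant is healthy tissue. These limit drift but do not remove group-linked expectation from a pooled AUC.
- **The size is assumed.** A reader might quote a larger figure by scoring group membership itself against the label: 0.5 + 0.5 × 0.125 = 0.563 at 10% drift. Group is not a candidate biomarker, so this is an upper limit. It falls to 0.554 if labels in the Achilles group do not drift.
- **The fiducial wording does not show unblinding.** MRI says that "fiducial markers will be placed over the marked trigger points identified during clinical examination". A reader might conclude that markers reveal the label and that healthy sites have no region of interest. But every zone is marked with the same cross, the ultrasound section refers to five marks, and the MRI section ties its regions to the examined locations. The phrase reads as shorthand.
- **Reordering now would do harm.** With 55 of 100 enrolled by November 2025, moving palpation ahead of the movement tasks would split the reference standard between early and late participants. This objection stands.

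**Conclusion.** The concern holds as a risk to the reference label, not as a demonstrated bias. The article has one therapist role run tasks that depend on knowing the painful site and then set the label. Its stated blinds leave that examiner, and group, uncovered. The direction is predictable: biomarkers that differ by group gain.

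The amount is unknown. Under the assumed 25% prevalence and 10% to 20% drift, it is about 0.02 to 0.07 of AUC for group differences of 0.5 to 1.2 SD. That could reorder close candidates but would not alone lift a useless biomarker to 0.70. The documents do not support a claim that the primary result is invalid, or that masking is absent from the study as a whole. This is a modest weakness that can be examined cheaply with data already being collected.

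**What to change.** 1. Report the AUC and the biomarker ranking within group, or adjusted for group by comparing only positive and negative sites from the same group, beside the pooled AUC. This is feasible for all participants. It does not remove drift tied to individual symptoms within a group.
2. Add a sensitivity analysis that ranks biomarkers against pressure pain threshold at the same five marks, relative to the participant's own mean. The participant triggers this measurement and it is already collected, although it belongs to the same examination. A biomarker with a single value per participant cannot be assessed this way.
3. Use coded IDs so that region-of-interest, strain and thickness measurements not yet made are done without knowledge of group. Leave out the radiologist's read, whose purpose is differential diagnosis in plantar heel pain.
4. Add examiner expectation to Limitations.

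Keep the present order of palpation and movement tasks.

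The cost is one extra set of analyses and some file coding, with no new staff or visits. Intervals are wider within group: the half-width for plantar heel pain alone is about 0.121, against the planned 0.10. Pressure pain threshold captures tenderness but not the taut band, so it supplements the palpation label and does not replace it.
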